To estimate the adjusted intervention effect while accounting for repeated measurements within individuals and potential confounding, mixed‐effects linear regression models with random intercepts for participants will be fitted for each outcome. Fixed effects included group (intervention vs. comparison), time (baseline vs. endline), and the group‐by‐time interaction, with the interaction term representing the DiD estimate of the intervention effect. Models will adjust for clinically relevant covariates, including age, sex, religion, marital status, educational level, residence, WHO clinical stage, opportunistic infections, treatment interruption, alcohol use, smoking status, and condom use. Adjusted beta (β) coefficients with their corresponding 95% confidence intervals (CIs) were reported.

Model assumptions, including normality of residuals, linearity, homoscedasticity, independence of observations, and multicollinearity, were evaluated before model interpretation. Random‐effects assumptions will be assessed using the estimated variance components and intraclass correlation coefficient (ICC). All statistical tests were two‐sided, and statistical significance will be declared at *p* < 0.05.

Because this is a pilot quasi‐experimental study with a relatively small sample size, greater emphasis will placed on the magnitude and precision of the estimated intervention effects, expressed as adjusted β coefficients and 95% confidence intervals, rather than statistical significance alone. These findings are intended to inform the design and sample size estimation of future adequately powered randomized or multicenter intervention studies.

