**Methods and Analysis:**

This pilot quasi‐experimental study will employ non‐randomized intervention and comparison groups with baseline and 6‐month follow‐up assessments. A total of 120 participants (60 per group) will be enrolled from selected hospitals in North‐West Ethiopia. Participants in the intervention group will receive a structured patient‐centered education program integrated into routine ART services, while the comparison group will continue receiving standard care. Quantitative data will be entered into EpiData version 4.6 and analyzed using STATA version 18. Descriptive statistics will summarize baseline characteristics. Baseline differences between groups will be assessed using chi‐square tests for categorical variables and independent t‐tests or non‐parametric equivalents for continuous variables. The primary outcome will be the change in log‐transformed HIV viral load (log_10_ copies/mL) from baseline to the end of the 6‐month follow‐up period. The intervention effect will be evaluated using paired t‐tests, difference‐in‐differences analysis, and multivariable linear regression while adjusting for potential confounders, including age, sex, educational status, baseline viral load, duration of ART, and medication adherence. Virological suppression, defined as HIV viral load < 1000 copies/mL, will be assessed as a secondary clinical outcome. Secondary outcomes will include medication adherence, HIV‐HBV‐related knowledge, self‐management practices, and retention in care. Statistical significance will be declared at *p* < 0.05. A qualitative study will be conducted at the end of the intervention period to assess the feasibility, acceptability, and implementation potential of the intervention. Qualitative data will be collected through focus group discussions with adult people live with HIV, in‐depth interviews with healthcare providers, and key informant interviews with hospital leaders and program managers. Audio‐recorded interviews will be transcribed verbatim and analyzed using directed thematic analysis with MAXQDA version 20.

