#### Follow‐Up and Endline Survey

2.12.2

Data will be collected at two time points: baseline (enrollment) and at the end of the 6‐month follow‐up period. At both assessment points, trained research nurses will collect socio‐demographic, clinical, and behavioral information through participant interviews and abstraction of medical records. Information on clinic attendance, retention in care, and pharmacy medication refill history among participants receiving ART will also be obtained from patient medical records. HIV viral load data will be collected at baseline and at the scheduled 6‐month follow‐up visit using laboratory viral load testing reports or dried blood spot (DBS) samples, where applicable. In addition, data on medication adherence, Health Belief Model (HBM) constructs, self‐management practices, and HIV–HBV‐related knowledge will be collected using structured questionnaires. All primary, secondary, and exploratory outcome measures will be assessed using data collected at these two time points to enable comparison of changes over time between the intervention and comparison groups.

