This study has several methodological limitations. The intervention and control groups are recruited from only two health facilities, with one facility serving as the intervention site and the other as the control site. As a result, differences in outcomes may reflect not only the effect of the intervention but also underlying site‐specific characteristics, making it challenging to fully separate intervention effects from facility‐level influences. In addition, the inclusion of only two sites precludes the use of clustering‐adjusted analytical approaches such as mixed‐effects models or generalized estimating equations. Although multivariable analyzes will be performed to adjust for measured baseline differences between groups, residual confounding arising from unmeasured participant‐ or facility‐level factors may remain. Therefore, the study findings should be interpreted cautiously, taking into account the potential impact of unmeasured site‐specific influences.

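### With baseline covariates entered as main effects, the adjusted difference-in-differences from the two-visit mixed model is essentially the unadjusted one, so measured confounding of the change in viral load is not controlled

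*Protocol article*

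**What the plan says.** Data Analysis (2.15) states the purpose of the model: "To estimate the adjusted intervention effect while accounting for repeated measurements within individuals and potential confounding". The model has a random intercept per participant and fixed effects for group, time and group-by-time, "with the interaction term representing the DiD estimate of the intervention effect". On adjustment it says: "Models will adjust for clinically relevant covariates, including age, sex, religion, marital status, educational level, residence, WHO clinical stage, opportunistic infections, treatment interruption", followed by three behavioural items. That makes twelve named covariates. The section does not say whether they are baseline or visit-specific values, and it names no covariate-by-time interaction. It makes the adjusted coefficient and its 95% CI the emphasised result and the basis for sizing later studies.

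Follow-Up and Endline Survey (2.12.2) fixes two visits: "Data will be collected at two time points: baseline (enrollment) and at the end of the" 6-month period. It has socio-demographic, clinical and behavioural data taken at each: "At both assessment points, trained research nurses will collect" them.

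The Discussion (3) says that "multivariable analyzes will be performed to adjust for measured baseline differences between groups" and concedes residual confounding only from unmeasured factors. The abstract (Methods and Analysis) names another adjusted analysis, a multivariable linear regression on age, sex, education and "baseline viral load, duration of ART, and medication adherence".

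**The concern.** Each arm is one purposively chosen hospital (2.8), so the plan leans on covariate adjustment to make the comparison credible. In a two-visit model whose effect is the group-by-time term, a covariate can alter that effect only through the change between visits. Time-fixed covariates entered as main effects explain the level of viral load, not its change. The report would then present the raw difference-in-differences (DiD) as adjusted, and readers would believe that measured differences between the hospitals had been handled. A later trial could be sized on that estimate.

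**Working it through.** **Inputs from the article.** Two visits (2.12.2); 60 per group and 20% expected loss (2.7), so 60 × 0.80 = 48 pairs per group and 96 in all; random intercept with group, time and group-by-time (2.15). The article gives no figure for imbalance or covariate effects, so every simulation value below is an assumption.

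**1. Algebra.** For participant i with group g and time-fixed covariates x:

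- baseline: y0 = a + b·g + c·x + u + e0
- endline: y1 = a + b·g + t + d·g + c·x + u + e1
- change: y1 − y0 = t + d·g + (e1 − e0)

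The term c·x and the person effect u both drop out. With complete pairs, the person averages carry no separate information on d, because group and group-by-time are proportional there. Hence d is estimated by the mean change in the intervention group minus the mean change in the comparison group, whatever x contains.

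**2. What is left uncontrolled.** If x also affects the change by k per unit, the estimate has expectation d + k × (mean of x at the intervention site − mean of x at the comparison site). Main effects of x do nothing to the second term. Adding x-by-time, or regressing the change on g and x, removes it.

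**3. Simulation, complete pairs.** 150 data sets, 60 per arm, person SD 0.6, visit SD 0.5, true effect −0.30 log10. A binary covariate has prevalence 40% against 65% and lowers the endline value by a further 0.5 log10. The expected bias is 0.25 × (−0.5) = −0.125. Mean estimates:

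| Model | Estimate |
|---|---|
| group × time | −0.400 |
| plus covariate main effects | −0.400 |
| plus covariate-by-time | −0.277 |

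The largest difference between the first two over all data sets was 9e-15. In the data set inspected, the standard error was 0.1197 for both. The gap to the third row is −0.400 − (−0.277) = −0.123, against the −0.125 built in. The averages share the same draws and sit about 0.02 above their expected −0.425 and −0.30. That is roughly two Monte Carlo standard errors for the raw estimate (0.138/√150 = 0.011).

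**4. About 20% endline dropout.** The means were −0.408, −0.405 and −0.278. Main effects removed 0.003 of a gap of 0.130. The adjusted and raw estimates differed by a median of 0.011 and at most 0.054 log10. Incomplete participants add some between-person information, so equality is no longer exact.

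**5. One covariate entered as time-varying, complete pairs.** Treatment interruption was set to 50% in both groups at baseline, then 20% (intervention) and 45% (comparison) at endline, each interruption raising log10 viral load by 0.6. The mean moved from −0.553 to −0.400 (median absolute difference 0.146, largest 0.351). The shift of 0.153 matches 0.6 × (0.45 − 0.20) = 0.15. If the education caused the fall in interruptions, that 0.15 is part of its effect, and the adjustment removes it.

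**6. The two adjusted analyses side by side.** Section 2.15 has a mixed model with twelve covariates, and its list names neither baseline viral load nor ART duration. The abstract has a linear regression with six covariates, including those two and medication adherence. Adherence is a secondary outcome that the counselling aims to change, and the abstract does not say which visit's value is meant. Neither analysis is named as primary.

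**The case against.** The strongest reply has four parts.

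- **Form and timing are not stated.** Section 2.15 is silent on both, and clinical and behavioural data are collected at both visits, so several covariates could enter as time-varying and the estimate would then move. This stands: a reader might infer that covariates can never change the estimate, and the documents do not support that. Equality is exact only for time-fixed covariates and complete pairs. Time-varying entry does not rescue the plan, because it adjusts for behaviour that the intervention targets.
- **DiD already deals with part of the site problem.** This also stands. A reader might infer that confounding by site is wholly untouched. That is wrong: stable level differences between the hospitals cancel. The Discussion also admits that site and intervention effects cannot be fully separated. What it does not admit is that measured differences affecting the change stay uncontrolled.
- **The abstract's regression might supply the adjustment.** Fitted to the change and with baseline covariates, it would. But it does not appear in 2.15, its covariates differ, it includes adherence, and it is not given priority. An article may leave detail to a fuller plan, but this is a conflict between two stated analyses.
- **Conditioning on baseline viral load is not a free improvement.** This stands too. It replaces the parallel-trends assumption of DiD. With an assumed stable site difference of 0.35 log10, parallel trends, no effect, and the SDs in step 3, the slope of endline on baseline is 0.36/(0.36 + 0.25) = 0.59. The baseline-adjusted contrast is then biased by (1 − 0.59) × 0.35 = 0.14, where plain DiD is unbiased.

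**Conclusion.** The point holds on the natural reading of 2.15, in which baseline covariates enter as main effects. The estimate reported as adjusted is then the raw DiD with complete pairs, and nearly so at the planned 20% loss. This contradicts the model's stated purpose in 2.15 and the assurance in the Discussion. The cancellation is algebraic and needs no assumption about imbalance. The size of the resulting bias does need one: zero if the sites are balanced on predictors of change, 0.125 log10 in the example in step 3, and 0.5 × 0.5 = 0.25 log10 for a covariate imbalanced by 0.5 SD that changes the 6-month response by 0.5 log10 per SD. None of these is a forecast for this trial. A reader might also infer that better adjustment would remove the site problem. It would not: with one hospital per arm, a hospital-specific trend cannot be separated from the intervention by any covariate model.

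**What to change.** In 2.15:

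1. State that covariates are baseline values only. Do not enter visit-specific treatment interruption, alcohol use or condom use.
2. Either add covariate-by-time terms to the mixed model, or regress the change in log10 viral load on group plus the baseline covariates (for example age, sex, education, ART duration and WHO stage). For these covariates the two give the same estimate with complete pairs.
3. Name this as the one primary adjusted model and bring the abstract into line with it, making clear that follow-up adherence is not a covariate.
4. Report the unadjusted DiD beside it.
5. Treat adjustment for baseline log10 viral load as a sensitivity analysis, in a change or endline regression. Do not enter it as a baseline-by-time term: baseline viral load is already a response in the mixed model, so that term would fit the baseline rows exactly and distort the variance estimates.
6. Amend the Discussion to say that adjustment covers only the listed baseline covariates and cannot remove a hospital-specific trend.

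The cost is a few lines of text and a few residual degrees of freedom out of about 96 pairs. The article already has age, sex, education, ART duration and WHO stage among its study variables, so no new data should be needed.

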##### Patient Demographics and Treatment Variables

2.12.2.1

A structured data abstraction form and interviewer‐administered questionnaire will be used to collect participants' socio‐demographic, clinical, behavioral, and treatment‐related information under the supervision of the research team, which includes the principal investigator, a statistician, a clinical pharmacist, and senior medical experts. Trained research nurses will collect the data, while the principal investigator will oversee data quality through regular monitoring and validation.

Variables to be collected include age, sex, duration since HIV diagnosis, duration on ART, baseline and follow‐up HIV viral load, CD4 count, HBV serological status, comorbidities, concurrent medications, medication adherence, Health Belief Model (HBM) constructs, retention in care, and HIV–HBV‐related knowledge scores. These variables will be recorded at baseline and reassessed at the 6‐month follow‐up to evaluate changes over time and estimate the effect of the intervention.

Data will be obtained from participant interviews, patient medical records, laboratory reports, pharmacy refill records, and health facility electronic databases where available. All collected data will be anonymized by assigning unique study identification numbers before analysis to ensure participant confidentiality. Electronic datasets will be securely stored on password‐protected computers accessible only to authorized members of the research team.

Ethical approval will be obtained from the Institutional Review Board of the University of Gondar. Written informed consent will be obtained from all participants before enrollment. Permission to use standardized questionnaires and assessment tools will be secured from the respective developers or authorized sources prior to data collection.

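### Covariates that are constant within a person cancel from the group-by-time term, so the section 2.15 model leaves the difference-in-differences estimate essentially unadjusted for baseline patient mix

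*Protocol article*

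**What the plan says.** Section 2.15 (Data Analysis) sets out the adjusted analysis for each outcome: a linear mixed model with a random intercept per participant. It has three fixed effects, namely study group, visit and the product of the two. The product carries the result: "with the interaction term representing the DiD estimate of the intervention effect". The stated aim is an adjusted effect that allows for repeated measurements and for potential confounding.

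The covariates follow as a plain list: "Models will adjust for clinically relevant covariates, including age, sex, religion, marital status, educational level, residence, WHO clinical stage", then opportunistic infections, "treatment interruption, alcohol use, smoking status, and condom use". That makes 12. No covariate-by-time term is named, and the section does not say at which visit the covariates are taken. It adds that more weight will be put on the adjusted coefficients and their 95% confidence intervals than on significance.

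Section 2.12.2 confirms that there are only two measurements: "Data will be collected at two time points: baseline (enrollment) and at the end of the" 6-month follow-up. Section 2.12.2.1 says of its own variable list: "These variables will be recorded at baseline and reassessed at the" 6-month visit.

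The Discussion says that multivariable analyses "will be performed to adjust for measured baseline differences between groups". The Abstract describes a different adjusted analysis: multivariable linear regression adjusting for age, sex, educational status, baseline viral load, duration of ART and medication adherence.

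**The concern.** There is one hospital per arm, assigned purposively (section 2.8), so patient mix may differ between arms. DiD removes stable differences in level. It does not remove differences in patient mix that affect how far viral load moves over six months, and covariate adjustment is the protocol's stated analytic protection against those. If covariates enter the section 2.15 model only as main effects, they adjust the difference in level, which DiD has already dealt with, and leave the estimated effect where it was. The coefficient that the protocol wants to emphasise, and to carry into the sample size of a later trial, would be labelled adjusted without having been adjusted for baseline mix. The same model is planned for every outcome, so adherence and knowledge scores are affected too.

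**Working it through.** The protocol states no figure on this point, so there is none to reproduce. The check is algebra, then simulation.

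**Algebra.** Let G be group, X the covariates (same value at both visits), u the participant intercept and θ the group-by-time coefficient.

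- Baseline: Y0 = a + bG + γX + u + e0
- Endline: Y1 = a + d + (b + θ)G + γX + u + e1
- Change: D = Y1 − Y0 = d + θG + (e1 − e0)

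Both γX and u cancel. With both visits observed, the estimate of θ is the mean change in the intervention group minus the mean change in the comparison group, whether or not X is in the model. If X also affects the change, D = d + θG + δX + error, and this estimate has expectation θ + δ × (mean X in intervention − mean X in comparison). The second part is removed only if the model contains δ, that is, a covariate-by-time term.

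**Simulation of the cancellation.** Assumed inputs: 60 per arm; two visits; age, sex, education and alcohol use imbalanced between arms; true effect −0.30 log10. Alcohol use shifts the change by +0.6 and education by −0.4, with group differences in proportion of −0.3 and +0.3. Expected bias: 0.6 × (−0.3) + (−0.4) × 0.3 = −0.30, so an unadjusted DiD should average −0.60. All mixed models were fitted by REML with a random intercept.

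| Data | No covariates | Main effects | Covariate × time | Change regressed on group + covariates |
|---|---|---|---|---|
| Complete | −0.610 | −0.610 | −0.312 | −0.312 |
| 20% random loss | −0.601 | −0.602 | −0.299 | −0.297 |
| 20% covariate-dependent loss | −0.581 | −0.589 | −0.298 | −0.296 |

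With complete data the first two columns differ by at most 9e-15 over 100 datasets, and the SE is 0.119 in both. With 20% loss (200 datasets per row) they differ by about 0.014 on average and 0.05 at most, against an SE of about 0.13. The confounding remains in both columns.

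**Re-measured covariates.** When alcohol use was entered at its value for each visit, it no longer cancelled. The estimate moved by up to 0.13 but averaged −0.630 with complete data, no closer to −0.30.

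**Illustrative size.** The protocol gives no log10-scale inputs, so these are assumptions: no true effect, residual SD of change 1.0 log10, one covariate with slope 0.4 log10 per SD, and 60 × 0.80 = 48 completers per arm.

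- Imbalance 0.5 SD: bias 0.5 × 0.4 = 0.20 log10
- Imbalance 0.3 SD: bias 0.3 × 0.4 = 0.12 log10
- SE of the unadjusted DiD: √(1.0² + 0.4²) × √(2/48) = 1.077 × 0.204 = 0.220

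Simulation (1,500 replicates) gave mean estimates of 0.196 and 0.129, with false-positive rates of 14.2% and 8.1% at p < 0.05. With the covariate in the change model these became −0.001 and 0.006, with rates of 4.6% and 4.7%. A separate run of 3,000 replicates gave 15% and 8.8% without adjustment.

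**The case against.** Several objections have force.

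- **Functional form.** Section 2.15 does not say in so many words that covariates enter as main effects only, and a fuller document may exist. But the section lists the fixed effects, names the one interaction it wants and then adds the covariates. Main effects is the ordinary reading, and nothing else in the article suggests another.
- **Which covariates.** A reader might infer that the cancellation holds for every listed covariate. The documents do not support that. Section 2.12.2 collects clinical and behavioural information at both visits, so opportunistic infections, treatment interruption, alcohol use, smoking and condom use could enter with updated values and would not cancel. Those would be post-intervention values, however, and would not adjust for baseline differences.
- **Exact equality.** A reader might also infer that adjusted and unadjusted results will be identical. That is exact only for participants with both visits. Under the 20% loss assumed in section 2.7 they are merely very close.
- **The Abstract's regression.** If run on the change in log10 viral load, it could adjust for baseline mix, and the Discussion's sentence may refer to it, since the sentence before says that two sites rule out clustering-adjusted approaches such as mixed models. So it cannot be said that the protocol contains no working adjustment. But section 2.15 specifies another model, and the two covariate lists share only age, sex and education.
- **Pilot status.** The Discussion warns of residual confounding from unmeasured participant or facility factors, and no choice of covariate terms removes a pure hospital effect. That caveat does not cover measured factors that the protocol says it adjusts for.

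**Conclusion.** The point stands on the ordinary reading of section 2.15. For covariates that do not change within a person (age, sex, religion, education, residence and any other held at its baseline value), the adjusted DiD equals the raw DiD in participants with both visits, and is nearly equal under the expected attrition. Measured differences in patient mix that affect the change are left in. The cancellation is algebraic and needs no assumption about the data.

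The size of the resulting bias is a different matter. The 0.12 to 0.20 log10 and the false-positive rates of roughly 8% to 15% show what could happen under an assumed imbalance, slope and residual SD. They are not predictions for this trial, and a reader should not take them as such. If the listed covariates are balanced between hospitals, or do not predict the change, the bias from this source is nil.

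**What to change.** In section 2.15, fix every covariate at its baseline value and enter each with its time interaction. Equivalently, for participants with both visits, regress the change in log10 viral load on group plus the baseline covariates. Use a short list chosen in advance for expected influence on viral load change, because each interaction uses at least one degree of freedom and only about 96 completers (120 × 0.80) are expected. Treat the other outcomes in the same way.

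Do not substitute a regression of the endline value alone: without baseline viral load that is a post-only comparison. A model that also conditions on baseline viral load is ANCOVA, a different estimator that need not agree with DiD in non-randomised groups. If it is wanted, name it as such.

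Report the unadjusted DiD beside the adjusted one, and reconcile the Abstract, section 2.15 and the Discussion so that they describe one adjusted model and one covariate list.

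No new data are needed. The cost is a few degrees of freedom and possibly a slightly wider interval: in the simulations the SE went from 0.219 to 0.216 with a strong covariate and from 0.207 to 0.216 with a weak one.
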